#### Group assignment

All patients undergoing radiotherapy for breast cancer will be assessed for eligibility criteria (including the dose of radiation) immediately after the radiotherapy planning. Eligible patients will be informed about the study and invited to participate. A total of 52 patients undergoing radiotherapy for breast cancer (stages I to III) will be prospectively enrolled after providing informed consent.

The participants will be allocated to an intervention group (laser therapy, n = 26) or a to a control group (placebo, n = 26). The latter will receive treatment from a deactivated laser unit that does not deliver radiation.

Group allocation will be determined using randomly generated computer sequences (Software R™, R Foundation for Statistical Computing, Vienna, Austria) [22]. The allocation concealment will be achieved by using a sealed opaque envelope with patient’s number in the study, which will be opened by the physiotherapist responsible for the intervention immediately before the first laser or placebo application.

The radiotherapist, the oncologist, the nurse, and the patients will be blinded to the allocation outcome. Only those administering the intervention (physiotherapist) will know the allocation of patients into the groups.

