The CTC was first described in 1982 and the version we will is the 4.0. It classifies radiodermatitis in degrees: 1 (faint erythema or dry desquamation), 2 (moderate to brisk erythema; patch moist desquamation, mostly confined to skin folds and creases; moderate edema), 3 (moist desquamation in areas other than skin folds and creases; bleeding induced by minor trauma or abrasion), 4 (life-threatening consequences; skin necrosis or ulceration of full thickness dermis; spontaneous bleeding from involved site; skin graft indicated) and 5 (death) [24].

Also in 1982, The RTOG developed the Criterion score for Acute Radiation Morbidity - Acute Radiation Morbidity Scoring Criteria, to classify the effects of radiotherapy. This criterion identifies grades 0 (no change over baseline), 1 (follicular faint or dull erythema, epilation, dry desquamation, decreased sweating), 2 (tender or bright erythema, patchy moist desquamations, moderate edema), 3 (confluent, moist desquamation other than skin folds, pitting edema) and 4 (ulceration, hemorrhage, necrosis) [5].

The visual analogue scale for pain was adapted and validated for use in Brazil by Ferraz *et al*. [23], in 1990. It is a patient self-evaluation scale, ranging from 0 to 10, with 0 meaning no pain and 10 meaning maximum pain [23].

Grading of radiodermatitis and pain assessment and will be repeated 90 days after the beginning of radiotherapy. If any of the evaluators perceive any adverse event that could be attributed to the intervention, or if the patient withdraws consent at any time, this patient will be immediately withdrawn from the study.

Both arms will follow the institutional skin care protocol, which consists of chamomile cream 10% with silicone cream 5.5%. This concoction will be used three times a day for the duration of the radiotherapy.

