#### Outcome measures

The primary outcome is assessment and grading of radiodermatitis. The secondary outcome is pain assessment.

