#### Endpoints

Participation is in this study is considered complete 90 days after the beginning of radiotherapy. However, exit points include a delay in radiotherapy greater than 10 days (if the break is not caused by radiodermatitis), or non-attendance of the patient at weekly review sessions.

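### The adverse-event and missed-review rules take patients out of the study altogether, so the primary outcome can itself end its own measurement

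*Protocol article*

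**What the plan says.** Three rules in the protocol article end a patient's participation early for reasons other than withdrawn consent.

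- **Adverse event** (Baseline procedures and interventions): "If any of the evaluators perceive any adverse event that could be attributed to the intervention", then "this patient will be immediately withdrawn from the study". One evaluator is enough, any event qualifies, and possible attribution suffices. The same sentence gives withdrawal of consent the same consequence.
- **Missed reviews** (Endpoints): "non-attendance of the patient at weekly review sessions" is an exit point. No number of misses is given and there is no exemption.
- **Delay** (Endpoints): "exit points include a delay in radiotherapy greater than 10 days (if the break is not caused by radiodermatitis"). This is the only rule that mentions radiodermatitis, and it protects patients whose break was caused by it.

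Under Outcome measures, "The primary outcome is assessment and grading of radiodermatitis". CTC grade 3, the event behind the sample size, is "moist desquamation in areas other than skin folds and creases; bleeding induced by minor trauma or abrasion". Skin is graded weekly after the second week until treatment ends, and again 90 days after radiotherapy starts. Participation is "considered complete 90 days after the beginning of radiotherapy". On blinding, Group assignment says: "The radiotherapist, the oncologist, the nurse, and the patients will be blinded to the allocation outcome".

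**The concern.** The laser or placebo probe is applied to breast or chest-wall skin, on a grid laid over the treated area. The three evaluators who grade that skin are also the people who judge whether an adverse event could be due to the intervention. Moist desquamation or bleeding in that field is thus both a primary-outcome event and something an evaluator could reasonably think the intervention may have caused. A patient with a painful reaction may also miss a review.

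The consequence is removal from the study, not only from laser or placebo application. Later weekly grades and the 90-day grade are then not collected. This matters in two situations:

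- A patient is removed at a lower grade and would have gone on to grade 3, which is never observed.
- A patient misses the review because of the reaction, so there is no grade at the moment of exit.

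In both, whether the outcome is missing depends on the outcome. With 26 patients per arm, a few such losses are enough to matter.

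**Working it through.** **Step 1. Set the three exits side by side.**

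| Exit | Can radiodermatitis trigger it? | Exemption |
|---|---|---|
| Adverse event possibly due to intervention | Yes, on the wording | None |
| Missed weekly reviews | Yes, indirectly | None |
| Delay over 10 days | No | Breaks caused by radiodermatitis |

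The article keeps patients in when radiodermatitis causes a break, yet leaves open their removal when an evaluator thinks the same reaction could be due to the intervention.

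**Step 2. Reproduce the sample size.** Inputs from Sample size: control rate p1 = 0.3522, laser rate p2 = 0.0762, one-tailed 5%, power 80%. The mean rate is p̄ = (0.3522 + 0.0762)/2 = 0.2142.

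n per arm = [1.645 × √(2p̄(1−p̄)) + 0.8416 × √(p1(1−p1) + p2(1−p2))]² / (p1−p2)²
= [1.645 × 0.5802 + 0.8416 × 0.5464]² / 0.276² = 26.3, rounded up to 27.

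The stated 26 agrees to within one patient. One-sided power at 26 per arm is 79.6% by this normal approximation. It is 82.6% when the pooled z-test is enumerated over all binomial outcomes. Enrolment is 52 = 2 × 26, so there is no margin for loss.

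**Step 3. Illustrate the loss.** The article gives no removal rate, so the fraction f is an assumption. Suppose f of the grade 3 patients in each arm leave and their grade is not counted. Then:

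- patients left in an arm: 26 × (1 − f·p)
- observed rate: p(1 − f)/(1 − f·p)

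With d the observed difference, the normal-approximation power is Φ[(d − 1.645·s0)/s1]. Here s0 is the pooled and s1 the unpooled standard error at the reduced arm sizes.

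| f | Control: n, rate | Laser: n, rate | Difference (points) | Power, normal | Power, enumerated |
|---|---|---|---|---|---|
| 0 | 26.0, 35.2% | 26.0, 7.6% | 27.6 | 79.6% | 82.6% |
| 10% | 25.1, 32.9% | 25.8, 6.9% | 25.9 | 76.3% | 79.3% |
| 25% | 23.7, 29.0% | 25.5, 5.8% | 23.1 | 70.2% | 73.6% |
| 50% | 21.4, 21.4% | 25.0, 4.0% | 17.4 | 56.9% | 60.0% |

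For f = 50%: (0.1741 − 1.645 × 0.0956)/0.0968 = 0.17, and Φ(0.17) is about 57%. That case removes 26 × 0.3522 × 0.5 = 4.6 control patients and 26 × 0.0762 × 0.5 = 1.0 laser patient on average.

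**Step 4. Loss unrelated to the outcome.** The exits also cost power when removal has nothing to do with the skin. On the normal approximation, 23 analysed per arm gives 75.0% and 21 gives 71.5%.

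**The case against.** The case on the other side has four parts.

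**The rule may not mean radiodermatitis.** The article attributes radiodermatitis to radiation throughout, so the adverse-event rule may be meant for other harms of the laser. That is plausible, but the wording is any adverse event that could be attributed, and only the delay rule carries an exemption. Removal through the outcome is permitted by the text; it is not stated to happen.

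**The grade may already be recorded.** Evaluators who trigger removal will normally have just graded the skin, and nothing says that earlier grades are discarded. This stands. If the triggering grade counts, the loss modelled above disappears for patients already at grade 3. It does not disappear for those removed at a lower grade or after a missed review.

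**The analysis set may be defined elsewhere.** A reader might infer that the comparison is no longer of the randomised groups. The article does not say so, and an analysis plan that is not shown may define the population. But no such plan can supply gradings that were never made, and the withdrawal rule is stated text, not an omission.

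**Blinding.** A reader might infer bias in favour of the laser. If there is no true effect (21.42% in both arms), dropping 25% or 50% of laser-arm events and no control events would raise the one-sided false-positive rate to about 10.6% or 21.6%. The arithmetic is right, but with blinded evaluators and no effect on skin there is no mechanism for one-sided removal, so these figures are not relied on. Blinding does not prevent removals, however: evaluators respond to the skin, and if the laser changes the skin, removal rates may differ between arms.

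A reader might also count the 10-day delay as removal by the outcome. Its exemption says the opposite. It remains an exclusion after randomisation, for other reasons.

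**Conclusion.** The point holds for two of the three exits. As written, the adverse-event rule and the missed-review rule end study participation, and either can be set off by the primary outcome. The delay rule is an exclusion after randomisation but not removal by the outcome, and its exemption makes the two sections inconsistent on radiodermatitis.

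The direction of bias is uncertain. The size is unknown, because no removal rate is given. The fall in one-sided power from about 83% to between 79% and 60% rests on three assumptions: the article's planning rates, equal removal fractions of 10% to 50% in both arms, and grades that are not counted. It shows the sensitivity of a 52-patient trial and is not a forecast. The loss of later gradings needs none of these assumptions: it follows if withdrawal from the study means what it says.

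**What to change.** Reword the withdrawal sentence in Baseline procedures and interventions and the exit points in Endpoints so that these events do not end outcome assessment:

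- Whatever clinical decision is made about the laser or placebo, which this change leaves as it is, weekly grading and the 90-day assessment continue unless the patient withdraws consent to follow-up.
- The grade at the triggering visit counts in the primary outcome.
- Patients are compared in the groups to which they were randomised.
- The two sections are reconciled on whether radiodermatitis falls under the adverse-event rule.

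The cost is an amendment to the wording and a few extra gradings, mostly of patients who still attend for radiotherapy. Trial status reports 26 patients enrolled by the end of June 2014 with recruitment ongoing, so on that date half of the planned 52 were still to come.

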#### Outcome measures

The primary outcome is assessment and grading of radiodermatitis. The secondary outcome is pain assessment.

#### Endpoints

Participation is in this study is considered complete 90 days after the beginning of radiotherapy. However, exit points include a delay in radiotherapy greater than 10 days (if the break is not caused by radiodermatitis), or non-attendance of the patient at weekly review sessions.

#### Statistical analysis

Statistical analyses will be performed using Statistical Package for Social Sciences (SPSS) software v.18 (SPSS Inc., Chicago, Illinois, United States) and Software R™, (R Foundation for Statistical Computing, Vienna, Austria) [25]. The rejection level for the null hypothesis will be fixed at 5% (α ≤0.05). The pondered kappa coefficient will be used to compare responses among evaluators. The McNemar test will be used to compare levels of pain between groups (one test will be performed weekly). For inter-group assessments of the proportion of radiodermatitis, the Chi-square test will be used to compare group intervention and control.

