#### Study design and setting

This is a two-arm, parallel group, randomized controlled trial that will be conducted at the Hospital do Cancer de Barretos (Brazil), which treats annually approximately 600 patients who undergo adjuvant radiotherapy. Patients will be recruited from the radiotherapy department of this hospital.

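### Pain is to be compared between two unmatched arms with the McNemar test, a paired binary test that fits neither the design nor the 0–10 score

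*Protocol article*

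**What the plan says.** All of the following comes from the protocol article.

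- **Test for pain** (Statistical analysis): "The McNemar test will be used to compare levels of pain between groups (one test will be performed weekly". No other analysis of pain is named.
- **Significance level** (same section): "The rejection level for the null hypothesis will be fixed at 5" per cent.
- **Design** (Study design and setting): "This is a two-arm, parallel group, randomized controlled trial".
- **Allocation** (Group assignment): "The participants will be allocated to an intervention group (laser therapy, n = 26) or a to a control group (placebo, n = 26"; and "Group allocation will be determined using randomly generated computer sequences". No matching, crossover or within-patient control is described.
- **Pain scale** (Baseline procedures and interventions, text after Figure 1): "ranging from 0 to 10, with 0 meaning no pain and 10 meaning maximum pain". No cut-off is stated.
- **Status of pain** (Outcome measures): "The secondary outcome is pain assessment".

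For radiodermatitis, the sentence right after the McNemar sentence compares the same two groups with a chi-square test, which is an independent-samples method.

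**The concern.** The McNemar test asks whether a yes/no response differs between the two members of a pair: the same patient on two occasions, or two deliberately matched patients. It uses only the discordant pairs. This trial has no pairs between arms and no yes/no pain variable. The same short section therefore treats the two arms as unpaired for radiodermatitis and as paired for pain.

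An analyst who follows the sentence must invent two things: which laser patient goes with which placebo patient, and where to cut the score. The first makes the p-value depend on something as empty as the row order of the data file. The second discards information in a trial of 52 patients. What is at stake is the trial's answer on its only secondary outcome.

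**Working it through.** **1. Requirements against design**

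| McNemar needs | The article gives |
|---|---|
| Paired or matched observations | 26 and 26 different patients, randomised individually |
| A binary response | A 0–10 score with no cut-off |
| A contrast within pairs | A contrast between groups |

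Extensions of McNemar to more than two categories still need pairs. A within-patient use (one week against another, score dichotomised) would be legitimate, but it measures change over time and not the effect of the laser.

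**2. How far the pairing alone moves the result**

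The article gives no pain data, so assume 16 of 26 patients in one arm and 8 of 26 in the other have pain. Let k be the number of arbitrary pairs in which both patients have pain. The discordant counts are b = 16 − k and c = 8 − k. The exact two-sided p is 2 × P(Bin(b + c, ½) ≤ c). Under random pairing, P(k) = C(16,k) × C(10,8−k) / C(26,8).

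| k | b, c | Exact p | Share of pairings |
|---|---|---|---|
| 0 | 16, 8 | 0.152 | <0.1% |
| 1 | 15, 7 | 0.134 | 0.1% |
| 2 | 14, 6 | 0.115 | 1.6% |
| 3 | 13, 5 | 0.096 | 9.0% |
| 4 | 12, 4 | 0.077 | 24.5% |
| 5 | 11, 3 | 0.057 | 33.6% |
| 6 | 10, 2 | 0.039 | 23.1% |
| 7 | 9, 1 | 0.021 | 7.3% |
| 8 | 8, 0 | 0.008 | 0.8% |

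Share below 0.05: 23.1% + 7.3% + 0.8% = about 31%. The other 69% or so are not significant, on identical data.

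Unpaired tests give one answer each. Chi-square without correction: 52 × (16×18 − 10×8)² / (26×26×24×28) = 4.95, p = 0.026. Fisher's exact test: p = 0.050.

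**3. Error rate and power with 26 per arm (simulation)**

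- With no true difference, exact McNemar on arbitrary pairs rejects in about 2.4% of trials at a nominal 5%. The test is conservative.
- With an assumed true difference of 0.7 SD: t-test on the score about 70%; median split with unpaired chi-square about 49%; median split with exact McNemar about 39%. Cutting the score costs about 21 percentage points, and the arbitrary pairing about 10 more.

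**4. Weekly repetition (minor)**

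The number of tests is not stated. Radiotherapy runs 25 to 30 sessions at five a week: 25/5 = 5 to 30/5 = 6 weeks. Assessment starts after week 2, which gives 3–4 weekly tests if the first visit is in week 3, or 4–5 if it is at the end of week 2. Adding day 90 gives up to 6. For valid tests at 5%, the chance of at least one false positive is:

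- independent: 1 − 0.95³ = 14% to 1 − 0.95⁶ = 26%;
- assumed correlation 0.7 between weeks (simulated): about 11% to 16%.

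**The case against.** It can be said that this is a condensed article, that a full analysis plan may exist, and that the error touches only the secondary outcome. The last part is right: the chi-square analysis of radiodermatitis, the sample size and the data collection are untouched. But the pain test is not a detail left for later. It is a method stated for a named comparison, and nothing else in the article repairs it.

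A reader might infer more than the document supports, in four ways.

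- **That the weekly tests are an equal defect.** Pain is secondary, and an adjustment or a key time point may sit in an analysis plan that is not shown. The article does not say that significance in any one week will count as success.
- **That the stated plan carries a 14–26% false-positive risk.** Those figures assume tests with a true size of 5%. At the 2.4% found above, three to six independent tests give 1 − 0.976³ = 7% to 1 − 0.976⁶ = 14%. The fault of McNemar here is arbitrariness and lost power, not excess false positives.
- **That p-values as far apart as 0.008 and 0.152 are typical.** Both extremes are rare. About 81% of pairings give p between 0.039 and 0.077. That range still straddles 0.05.
- **That one particular model is required.** Any sound independent-groups analysis of the score cures the error.

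**Conclusion.** Wrong as written. The only between-group pain test named is a paired binary test, applied to two independent arms and a 0–10 score. This follows from the text and rests on no assumption.

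The size is illustrative. It depends on the assumed 16/26 against 8/26 split, the assumed 0.7 SD difference and a median cut, none of which comes from the article. On those inputs the same data are significant in about 31% of pairings and not in the rest, and power falls from about 70% to about 39%.

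The consequence is confined to the secondary outcome, where a real reduction in pain would be more likely to be missed. The weekly repetition is a minor, separate remark, and the count of about 3 to 6 tests behind it is an inference.

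**What to change.** Replace the McNemar sentence with an independent-groups analysis of the 0–10 score that names one main comparison. Either of these would do:

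- a Mann-Whitney test between the randomised groups on each patient's worst pain score; or
- a mixed model over all visits (group, week, group by week, patient effect) with one pre-specified group contrast, reported with a 95% confidence interval.

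If the model is chosen, fix the contrast with the course of the reaction in mind. The Background describes reactions that develop over weeks, so a plain average over all visits could dilute a late effect.

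State that week-by-week results are descriptive or, if tested, adjusted (Holm, for example).

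The cost is one or two sentences. Pain is already collected weekly and at day 90, so no extra data, patients or procedures are needed. Recruitment was still under way when the article was written (26 patients enrolled by the end of June 2014), so the change could be made before any analysis.

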## Discussion

Radiodermatitis is one of the most common side effects of radiation therapy, and despite advances in treatment techniques, skin reactions remain inevitable [1, 26]. Moreover, this adverse event can represent a significant source of pain or discomfort and can lead to limited daily activities, a decrease in quality of life, decreased patient adherence to treatment, or even an interruption of treatment [1]. Consequently, it is important that efforts be made to prevent radiodermatitis.

Low-power laser treatments have been well-established for the prevention and treatment of oral mucositis and for the treatment of lymphedema [12–15, 17–20]. Moreover, according to a recent meta-analysis on radiation-induced mucositis, low-level laser therapy at a dose of 2 to 3 J/cm [2] that was administered in daily applications, or at least three times a week, did not result in any adverse effects [14].

Regarding lymphedema, a recent systematic review presented moderate to strong evidence that low-level laser treatments are effective for the management of this condition [17]. For the 230 patients analyzed, a dose of 1 to 2 J/cm [2] per point applied, with several points covering the fibrotic area, reduced limb volume [17]. Furthermore, Carati *et al*. [20] conducted a prospective, double-blind, randomized controlled study with 61 patients who underwent mastectomy and then developed lymphedema. There were 28 patients in the placebo group and 33 patients in the treatment group. For the latter, a 904 nm RianCorp LTU 904H laser was applied to 17 points at 2 cm intervals (using a plastic guide) in the region of the axilla for each patient. For the placebo group, the laser unit was deactivated and no radiation was delivered. Moreover, this unit was indistinguishable from the active unit. The total energy applied was 1.5 J/cm [2], and this treatment was found to reduce the volume of arm lymphedema in 31% of the patients that completed three months of this treatment [20].

Despite all the training conducted for the grading of radiodermatitis, the CTC and RTOG’s scales are dependent on observers, and this may lead to a grading bias. Unfortunately we cannot completely eliminate subjectivity in evaluating the radiodermatitis grade.

In the absence of clinical guidelines for the prevention of radiodermatitis, treatment of this side effect of radiation remains a challenge. However, based on the effectiveness of laser treatments for the prevention of oral mucositis, a clinical trial to investigate the beneficial application of laser treatments as a prophylaxis for radiodermatitis was established. It is possible that the results of this trial may provide a standard treatment for the prevention of acute skin reactions that develop following radiotherapy.

